### Trial interventions

#### Active therapy

The active therapy is Salovum®, an egg yolk powder enriched for AF, which is manufactured from freeze-dried egg yolk (Lantmännen Functional Foods AB, Stockholm, Sweden).

#### Placebo therapy

A placebo powder, containing low amounts of antisecretory factor, made from freeze-dried egg yolk and identical in taste, texture, smell, and color to Salovum®, will be used. The placebo powder is manufactured and supplied by Lantmännen Functional Foods AB.

#### Dosage

Salovum® or placebo egg powder will be administrated for 5 days. The trial substance is administered according to 1 g per patient kg body weight per 24 h, divided into 6 dosages, administered every 4 h. The study site is equipped with digital scales for weighing the trial substance before administration.

#### Dispensing

Both the Salovum® and placebo substance are packaged in identical bags by Lantmännen Functional Foods AB. After opening of a bag, each containing 20 g, a weighed aliquot depending on patient weight will be mixed with 50–100 ml tap water in a glass container. Electrical milk frothers are used for mixing. The mixture will then be aspirated into a syringe and administered to the patient via the nasogastric tubing, used for enteral nutrition.

#### Protocol adherence

Protocol adherence will be encouraged via monitoring and daily inspections by investigators and/or research nurses. Any important protocol modifications will be promptly communicated to all study investigators and research nurses.

#### Study endpoints

The primary endpoint is the effect of AF, given as a dietary supplement in the form of Salovum®, compared with placebo on ICP [24]. The secondary endpoint is the effect on inflammatory mediators [25] in patients with severe TBI. Exploratory endpoints include intracerebral oxygen pressure (PbtO_2_) [26], cerebral perfusion pressure (CPP), mortality at 30 days, therapy intensity level (TIL, see page 9) [27, 28], brain metabolites [29, 30], ICP change from baseline, ICP under the curve and outcome according to the extended Glasgow Outcome Scale (eGOS) at 6 months. Binary outcome variables (i.e., 30-day mortality) will be analyzed using the chi-square test. For continuous data, the Mann–Whitney *U* test will be used. All computations will be run with the free statistical software R (https://www.r-project.org).

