**Methods/design:**

This is a single-center, randomized, placebo-controlled clinical phase 2 trial, investigating the clinical superiority of Salovum® given as a food supplement during 5 days to adults with severe TBI (Glasgow Coma Scale (GCS) < 9), admitted to the neurocritical intensive care unit (NICU) at Skane university hospital, Lund, Sweden. All patients with GCS < 9 and clinical indication for insertion of ICP-monitor and microdialysis catheter will be screened for inclusion and assigned to either the treatment group (*n* = 10) or placebo group (*n* = 10). In both groups, the primary outcome will be ICP (mean values and change from baseline during intervention), registered from high-frequency data monitoring for 5 days. Secondary outcomes will be inflammatory mediators in plasma and intracerebral microdialysis perfusate days 1, 3, and 5 during trial treatment.

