#### Data collection of outcome parameters and predefined covariates

Basic parameters (GCS, GCS-T, age, gender, medical history, diagnosis) are collected from electronic medical charts (Melior) and the monitoring system (IntelliSpace Critical Care and Anesthesia [ICCA] system; Philips) at the NICU. High-frequency data collection of physiological parameters (ICP, CPP, PbtO_2_, pulse, blood pressure, PO_2_, temperature) are sampled with a Moberg® CNS monitor. Brain metabolites (Lactate/pyruvate ratio, glucose, glutamate, glycerol) are analyzed using ISCUS flex (M Dialysis AB). All data from the Moberg CNS monitor and other electronic sources will be transferred to an electronic CRF (Redcap). TIL will be scored every 24 h. TIL will be recorded in a paper CRF and then transferred to the electronic CRF continuously., Plasma samples will be collected before the initial dose of the trial substance, thereafter twice daily for 5 days, and after the last dose of the trial substance. After centrifugation, aliquoted samples will be stored in a − 80 °C freezer. The plasma will be analyzed for markers of brain damage and cytokines/chemokines. Similarly, microdialysis perfusate fluid will be stored in a − 80 °C freezer and analyzed for cytokines/chemokines and markers for brain damage (see Tables 1 and 2). Age, gender, GCS, GCS-T, and trauma mechanism at inclusion, may be used as covariates in exploratory regression analysis. Medical charts are used to track 30-day mortality. Patients or next of kin are followed up by visits and/or telephone interviews at the outpatient clinic in order to assess eGOS > 6 months. All data is stored in a specific password-protected eCRF, only accessible to investigators (Fig. 1).

**Table 1 Tab1:** Primary and secondary outcome measures

Outcome measure	Measure description	Time frame	Objective
ICP mean	Measured by an intracranial pressure sensor	During intervention, 5 days	Primary
ICP area under curve	Measured by an intracranial pressure sensor	During intervention, 5 days	Primary
Inflammatory cytokine secretion	Interleukin-6 (Il-6), interleukin-8 (IL-8), Interferon-gamma inducible protein (IP10) and monocyte chemotactic protein (MCP-1) assessed from microdialysate and plasma by multiplex analysis	During intervention, 5 days	Secondary

**Table 2 Tab2:** Exploratory outcome measures

Outcome measure	Measure description	Time frame
Mortality	Mortality due to TBI	At 30 days and 12 months

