Morbidity	Assessed by Glasgow Outcome Scale Extended (GOSE)	At 6 and 12 months
Intracerebral oxygen partial pressure	Measured by an intracranial oxygen sensor	Change from baseline during intervention
Intracerebral oxygen partial pressure	Measured by an intracranial oxygen sensor	During intervention, 5 days
Treatment intensity level	Treatment intensity level (TIL) scale. Minimum 0 (no intervention to control intracranial pressure (ICP)), maximum 38 points (maximum efforts to control ICP)	Change from baseline during intervention
Treatment intensity level	Treatment intensity level (TIL) scale. Minimum 0 (no intervention to control intracranial pressure (ICP)), maximum 38 points (maximum efforts to control ICP)	During intervention, 5 days
Rate of cerebral metabolism	Lactate/pyruvate ratio assessed by online microdialysis	Change from baseline during intervention
Rate of cerebral metabolism	Lactate/pyruvate ratio assessed by online microdialysis	During intervention, 5 days
Concentration of brain damage markers	Glial fibrillary acidic protein (GFAP), neurofilament light protein (NFL), tubulin associated unit (TAU), and ubiquitin C-terminal hydrolase L1 (UCH-L1)	Change from baseline during intervention
Concentration of brain damage markers	Glial fibrillary acidic protein (GFAP), neurofilament light protein (NFL), tubulin associated unit (TAU), and ubiquitin C-terminal hydrolase L1 (UCH-L1)	During intervention, 5 days
ICP mean	Measured by an intracranial pressure sensor	Change from baseline during intervention
ICP area under curve	Measured by an intracranial pressure sensor	Change from baseline during intervention
Inflammatory cytokine secretion	Interleukin-6 (Il-6), interleukin-8 (IL-8), interferon-gamma inducible protein (IP10) and monocyte chemotactic protein (MCP-1) assessed from microdialysate and plasma by multiplex analysis	Change from baseline during intervention

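### The article gives ICP area under the curve and ICP change from baseline conflicting status, primary in one place and exploratory in another; only mean ICP over 5 days fits every statement

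*Protocol article*

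**What the plan says.** Four places in the protocol article assign a status to the ICP measures.

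- **Abstract, Methods/design:** "the primary outcome will be ICP (mean values and change from baseline during intervention), registered from high-frequency data monitoring for 5 days".
- **Study endpoints:** "The primary endpoint is the effect of AF, given as a dietary supplement in the form of Salovum®, compared with placebo on ICP". No summary measure is named. The exploratory list in the same paragraph includes "ICP change from baseline, ICP under the curve and outcome according to the extended Glasgow Outcome Scale (eGOS) at 6 months".
- **Table 1 (primary and secondary outcomes):** two rows carry the label primary, "ICP mean Measured by an intracranial pressure sensor During intervention, 5 days Primary" and "ICP area under curve Measured by an intracranial pressure sensor During intervention, 5 days Primary".
- **Table 2 (exploratory outcomes):** "ICP mean Measured by an intracranial pressure sensor Change from baseline during intervention" and "ICP area under curve Measured by an intracranial pressure sensor Change from baseline during intervention".

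The Statistical analysis section gives Mann–Whitney and Wilcoxon tests for continuous data and refers to Additional files 1 and 3 for detail. The article states no significance level. It calls the trial exploratory in the title and in the power section. It also states a superiority aim in the Abstract and under Trial design.

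**The concern.** A primary endpoint is labelled in advance so that the deciding result cannot be chosen after the data are seen. Here two ICP summaries have two statuses each. If AUC favours the active arm, Table 1 supports calling it primary; if it does not, the Study endpoints section supports calling it exploratory. The same holds for change from baseline, with the Abstract on one side and the Study endpoints section and Table 2 on the other.

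The ICP comparison carries weight. The Introduction says that a demonstrated effect would open a new therapeutic option, and the Discussion says that confirmation would support further use. A reader of the results needs to know which comparison was meant to bear that claim.

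**Working it through.** **Step 1. Status of each measure, side by side.**

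| Measure | Abstract | Study endpoints | Table 1 | Table 2 |
|---|---|---|---|---|
| Mean ICP during the 5 days | primary | not named; consistent with ICP as primary | primary | not listed |
| AUC during the 5 days | not listed | exploratory (time frame not given) | primary | not listed |
| Change from baseline in ICP | primary | exploratory | not listed | exploratory (mean) |
| Change from baseline in AUC | not listed | not separately named | not listed | exploratory |

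The first row contains no conflict. The second conflicts between Table 1 and Study endpoints. The third conflicts between the Abstract and both Study endpoints and Table 2. The AUC row of Table 2 is a change measure, so it does not contradict Table 1.

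**Step 2. Inputs for the error rates.** From the article: 10 patients per arm, Mann–Whitney test, no interim analysis. Assumed, because the article does not give them: two-sided 0.05 per test, normally distributed values, equal SD at baseline and during treatment, and the correlation r between baseline and on-treatment ICP. The article has no error-rate or power figure to reproduce.

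**Step 3. One endpoint.** At 10 against 10, the largest rejection region with size at most 0.05 is U ≤ 23 or its mirror image. Of the C(20,10) = 184,756 rank arrangements, 3,996 have U ≤ 23. The exact size is 2 × 3,996 / 184,756 = 0.0433.

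**Step 4. Upper reference.** Independent tests at 0.05 each give 1 − 0.95² = 0.0975 for two chances and 1 − 0.95³ = 0.1426 for three. The ICP measures are correlated, so the true values are lower.

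**Step 5. Mean or change from baseline.** With equal SDs, the correlation between mean and change is (1 − r)/√(2(1 − r)) = √((1 − r)/2), for example 0.5 at r = 0.5. Simulation of 60,000 null trials per setting, success on either:

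| r | mean or change |
|---|---|
| 0 | 0.073 |
| 0.3 | 0.078 |
| 0.5 | 0.080 |
| 0.7 | 0.082 |
| 0.9 | 0.085 |

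**Step 6. Mean or AUC.** AUC = mean × monitored duration. If every patient has the same duration, AUC is the mean times a constant, the ranks are identical and nothing is added: 0.043. If 10% of patients have monitoring cut to 72–120 h (assumed), the result is about 0.049 to 0.054. If 35% are cut to 24–120 h (assumed), it is about 0.07 to 0.075.

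**Step 7. Any of the three.** With equal durations this equals mean or change, 0.073 to 0.085. Under the 35% assumption it reaches about 0.10 to 0.11. No single section names three primaries, so this figure requires picking across sections.

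**The case against.** Several points on the other side are sound.

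- A reader might infer three mutually exclusive primary endpoints. The text does not go that far: mean ICP over 5 days is primary in the Abstract and Table 1, and nothing in Study endpoints or Table 2 makes it exploratory. The dispute is over what, if anything, stands beside it.
- A reader might infer that the trial has no control over multiple primaries. The article cannot show that. Additional file 1 is the full protocol, the analysis detail is placed in Additional files 1 and 3, and a multiplicity or co-primary rule may stand there. Its absence from a journal article is not a fault. The opposite labels within the article are a different matter: whatever those files say, the article's own statements disagree.
- A reader might infer that a stated 5% error rate is broken. The article states no significance level and calls the trial exploratory. That softens the consequence. It does not remove it, because a superiority aim is also stated and a primary endpoint is labelled.
- The AUC route may add nothing. The missing-data section expects few gaps and prescribes carrying the last observation forward or mean substitution. If that is applied to the ICP series of patients whose monitoring ends early, durations become equal and AUC ranks patients exactly as the mean does. The larger AUC figures therefore rest on an assumption about truncated monitoring that the article does not support.

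What remains is the labelling conflict for both measures, and for change from baseline an inflation that does not depend on monitoring time.

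**Conclusion.** The point holds as an internal contradiction over which ICP measures are primary. AUC and change from baseline each have two statuses; mean ICP over the 5-day intervention is the only measure compatible with every statement.

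In size, the firm result is mean or change: about 7% to 8.5% false positives against 4.3% for one endpoint, close to a doubling, across baseline correlations from 0 to 0.9. Mean or AUC runs from 4.3% to about 7%, depending wholly on unequal monitoring time. The 11% for any of three is the top of a range that starts at 7% to 8%, and should not be quoted alone. All figures assume two-sided 0.05 per test and no adjustment. They show what the ambiguity would allow, not what the trial will do.

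**What to change.** Before unblinding, name mean ICP over the 5-day intervention as the single primary endpoint in the Abstract, the Study endpoints section and Table 1. Label AUC and change from baseline exploratory in all of them, moving the 5-day AUC row from Table 1 to Table 2. Amend the registry entry if it differs; its content was not available for this check.

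If two ICP measures are to stay primary, say whether both must succeed. If either suffices, use Holm, or Bonferroni at 0.05 / 2 = 0.025 each, which keeps the total at or below 0.05.

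The cost is wording in a few places, with no new data or patients. Timing is the constraint: recruitment was estimated to end on December 30, 2024 and the article appeared on February 7, 2025, and the article does not say whether unblinding has taken place. If it has, and neither the full protocol nor the registry already fixes the choice, the trial report should give all three measures and disclose the discrepancy.

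Adjusting for baseline ICP is a separate, optional suggestion. It would replace the stated Mann–Whitney test and is not needed to resolve this point.

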#### Data collection of outcome parameters and predefined covariates

Basic parameters (GCS, GCS-T, age, gender, medical history, diagnosis) are collected from electronic medical charts (Melior) and the monitoring system (IntelliSpace Critical Care and Anesthesia [ICCA] system; Philips) at the NICU. High-frequency data collection of physiological parameters (ICP, CPP, PbtO_2_, pulse, blood pressure, PO_2_, temperature) are sampled with a Moberg® CNS monitor. Brain metabolites (Lactate/pyruvate ratio, glucose, glutamate, glycerol) are analyzed using ISCUS flex (M Dialysis AB). All data from the Moberg CNS monitor and other electronic sources will be transferred to an electronic CRF (Redcap). TIL will be scored every 24 h. TIL will be recorded in a paper CRF and then transferred to the electronic CRF continuously., Plasma samples will be collected before the initial dose of the trial substance, thereafter twice daily for 5 days, and after the last dose of the trial substance. After centrifugation, aliquoted samples will be stored in a − 80 °C freezer. The plasma will be analyzed for markers of brain damage and cytokines/chemokines. Similarly, microdialysis perfusate fluid will be stored in a − 80 °C freezer and analyzed for cytokines/chemokines and markers for brain damage (see Tables 1 and 2). Age, gender, GCS, GCS-T, and trauma mechanism at inclusion, may be used as covariates in exploratory regression analysis. Medical charts are used to track 30-day mortality. Patients or next of kin are followed up by visits and/or telephone interviews at the outpatient clinic in order to assess eGOS > 6 months. All data is stored in a specific password-protected eCRF, only accessible to investigators (Fig. 1).

**Table 1 Tab1:** Primary and secondary outcome measures

Outcome measure	Measure description	Time frame	Objective
ICP mean	Measured by an intracranial pressure sensor	During intervention, 5 days	Primary
ICP area under curve	Measured by an intracranial pressure sensor	During intervention, 5 days	Primary
Inflammatory cytokine secretion	Interleukin-6 (Il-6), interleukin-8 (IL-8), Interferon-gamma inducible protein (IP10) and monocyte chemotactic protein (MCP-1) assessed from microdialysate and plasma by multiplex analysis	During intervention, 5 days	Secondary

**Table 2 Tab2:** Exploratory outcome measures

Outcome measure	Measure description	Time frame
Mortality	Mortality due to TBI	At 30 days and 12 months
Morbidity	Assessed by Glasgow Outcome Scale Extended (GOSE)	At 6 and 12 months
Intracerebral oxygen partial pressure	Measured by an intracranial oxygen sensor	Change from baseline during intervention
Intracerebral oxygen partial pressure	Measured by an intracranial oxygen sensor	During intervention, 5 days
Treatment intensity level	Treatment intensity level (TIL) scale. Minimum 0 (no intervention to control intracranial pressure (ICP)), maximum 38 points (maximum efforts to control ICP)	Change from baseline during intervention
Treatment intensity level	Treatment intensity level (TIL) scale. Minimum 0 (no intervention to control intracranial pressure (ICP)), maximum 38 points (maximum efforts to control ICP)	During intervention, 5 days
Rate of cerebral metabolism	Lactate/pyruvate ratio assessed by online microdialysis	Change from baseline during intervention
Rate of cerebral metabolism	Lactate/pyruvate ratio assessed by online microdialysis	During intervention, 5 days
Concentration of brain damage markers	Glial fibrillary acidic protein (GFAP), neurofilament light protein (NFL), tubulin associated unit (TAU), and ubiquitin C-terminal hydrolase L1 (UCH-L1)	Change from baseline during intervention
Concentration of brain damage markers	Glial fibrillary acidic protein (GFAP), neurofilament light protein (NFL), tubulin associated unit (TAU), and ubiquitin C-terminal hydrolase L1 (UCH-L1)	During intervention, 5 days
ICP mean	Measured by an intracranial pressure sensor	Change from baseline during intervention
ICP area under curve	Measured by an intracranial pressure sensor	Change from baseline during intervention
Inflammatory cytokine secretion	Interleukin-6 (Il-6), interleukin-8 (IL-8), interferon-gamma inducible protein (IP10) and monocyte chemotactic protein (MCP-1) assessed from microdialysate and plasma by multiplex analysis	Change from baseline during intervention

**Fig. 1 Fig1:**
[figure not shown]
SPIRIT figure. * Intubated patients are evaluated using only the sum of eye opening and motor responses (GCS-T)

### Definition of outcome measures

#### Intracranial pressure (ICP)

ICP is measured with an inserted catheter for recording both intracerebral and, if possible, intraventricular pressure. Intracranial pressure measurement is a clinical routine in the treatment of severe head injury.

#### Cerebral tissue oxygen pressure (PbtO2)

PbtO_2_ is measured with inlaid probe (Licox, Integra) and is a clinical routine for a severe head injury.

#### RLS (Reaction Level Scale)

RLS is a certified scale for assessing the depth of unconsciousness and is a clinical routine for severe head injury in Nordic countries. The RLS scale goes from awake [1] to brain death/reactionless [8]. RLS can be translated as GCS.

#### GCS (Glasgow Coma Scale)

GCS is a certified scale for assessing the depth of unconsciousness in severe head injury internationally. GCS can be translated as RLS.

#### GCS-T

GCS-T is a modified GCS for intubated patients, evaluating only eye opening and motor responses.

#### Microdialysis of the brain

Microdialysis is done with thin, membrane-equipped catheters which are introduced into the brain tissue. Metabolic factors can be measured online and brain injury markers, inflammatory factors, etc. can be analyzed afterwards after the samples are frozen. Microdialysis is a clinical routine in severe head injuries. In this study, the lactate/pyruvate ratio and the glucose content are mainly analyzed.

#### Glasgow Outcome Scale - Extended (GOSE)

GOSE is a validated scale for estimating capacity and function in the follow-up of patients after head injury. The scale goes from 1 (dead) to restored 8 (good outcome).

#### Therapy Intensity Level (TIL)

TIL is a validated scale for estimating the measures taken to maintain normal intracranial pressure. The scale goes from no actions (0p) to full actions (38p). Low values indicate good control of ICP, high values indicate poor control of ICP.

#### Inflammatory mediators

Inflammatory cytokines are analyzed from microdialysates and blood using single and multiplex techniques; Mesoscale (Mesoscale Discovery) and O-link (O-link proteomics).

#### Brain injury markers

Brain injury markers, such as Nf-L, TAU, GFAP, and UCH-L1, are analyzed in blood and microdialysates using single ELISA or single/multiplex technique as described above.

#### Statistical power of proposed endpoints

This is an exploratory trial with no previous data to calculate power.

#### Statistical analysis

Binary outcome data (e.g., mortality) will be analyzed with the chi-square test. Continuous data will be analyzed using the Mann–Whitney *U* and Wilcoxon tests. Both per-protocol and intent-to-treat analyses will be performed. All statistical calculations will be conducted in R Studio. Please see Additional files 1 and 3 for detailed information.

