## Methods/design

### Trial design

This is a single-center, investigator-sponsored, phase 2, randomized, placebo-controlled, parallel-arm trial to assess the superiority of AF given as Salovum® in patients with severe TBI. The allocation ratio is 1:1. Recruitment commenced in March 2020.

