### Trial population and eligibility

A total of 20 patients with severe TBI will be enrolled at a single study site, Skane University Hospital, Lund Sweden. Patients with a Glasgow Coma Scale (GCS) score < 9 and clinical indication for insertion of ICP monitor, intracerebral oxygen pressure monitor (Licox®), and microdialysis catheter will be screened for inclusion.

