### Randomization

Patients in the trial are allocated to treatment with Salovum® or placebo egg yolk powder at a ratio of 1:1. The allocation sequence is generated by the principal investigator. Permuted block randomization, with blocks of 4–6, will be used and was compiled with R. Each patient is assigned a sequentially numbered study binder. The study number written in the binder corresponds to a sealed and opaque box with the same number, containing the study substance, either active (Salovum®) or placebo (normal egg yolk powder). Study substance and placebo appear identical with respect to packaging, color, texture, and smell. Investigators, caregivers, and patients are blinded during the entire trial. If any patient needs unblinding for medical reasons, an emergency unblinding list exists in digital form.

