#### Handling of missing data

With the exception of TIL, the data collected in this trial is limited to what is normally measured and registered during standard care at the NICU. Therefore, the amount of missing data is expected to be low. Data missing at random will be handled using the last observation carried forward (LOCF). Data not missing at random will be analyzed using mean substitution. If microdialysis is not initiated or fails after insertion, the patient will be given the trial substance or placebo as scheduled, but additional patients will be added in order to achieve 20 patients monitored with microdialysis data for a minimum of 3 days.

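### Mortality in about 20 patients is tested with an unspecified chi-square version, and Table 2 limits it to TBI deaths while the text names no cause

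*Protocol article*

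**What the plan says.** The article names the test twice. Statistical analysis has "Binary outcome data (e.g., mortality) will be analyzed with the chi-square test", and Study endpoints has "Binary outcome variables (i.e., 30-day mortality) will be analyzed using the chi-square test". Neither says whether a continuity correction is used. The software is R, and further detail is deferred: "All statistical calculations will be conducted in R Studio. Please see Additional files 1 and 3 for detailed information". Those files are not shown.

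The sample is small: "A total of 20 patients with severe TBI will be enrolled at a single study site", and "The allocation ratio is 1:1". Two provisions allow the final arms to differ from 10:10. Randomization says "Permuted block randomization, with blocks of 4–6, will be used and was compiled with R". Handling of missing data says that, if microdialysis is not started or fails, "additional patients will be added in order to achieve 20 patients monitored with microdialysis data for a minimum of 3 days".

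On the outcome itself, Study endpoints lists mortality at 30 days among the exploratory endpoints, and the data collection section says that it is tracked from medical charts. Neither names a cause. Table 2 describes the measure as "Mortality due to TBI" and gives two time points, 30 days and 12 months.

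**The concern.** The chi-square p-value is a large-sample approximation. With 10 per arm the smaller expected cell count cannot exceed 5, and it is well below 5 at most plausible death rates. The corrected and uncorrected versions are then two quite different tests, and R applies the correction to a 2×2 table unless told otherwise. An unstated option could therefore decide whether a mortality difference is reported as significant.

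The second issue is what counts as an event. Under Table 2, a patient who dies of something other than the brain injury is not an event; on a plain reading of the text that patient is. The article gives no rule for attributing cause. With 10 per arm, one reclassified death moves an arm's rate by 10 percentage points.

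**Working it through.** The article gives no alpha, power or mortality rate, so there is no stated figure to reproduce.

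**Inputs.** From the article: 20 patients, 1:1, chi-square test, R. Assumed: two-sided 0.05; death rates of 10% to 50%.

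**Step 1: expected counts.** Under equal death rates, expected deaths per arm are 10 × rate: 1 at 10%, 2 at 20%, 3 at 30%, 4 at 40%, 5 at 50%.

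**Step 2: one table by hand, 0/10 v 4/10 deaths.** With cells a, b in one arm and c, d in the other, ad − bc = 0×6 − 10×4 = −40, and the product of the margins is 10×10×4×16 = 6400.

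- Uncorrected: N(ad − bc)² / 6400 = 20×1600/6400 = 5.00, p = 0.025.
- Corrected: N(|ad − bc| − N/2)² / 6400 = 20×(40 − 10)²/6400 = 2.81, p = 0.094.
- Fisher: 2×C(10,4)/C(20,4) = 2×210/4845 = 0.087.

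Other tables behave alike (uncorrected, corrected, Fisher): 1/10 v 6/10 gives 0.019, 0.061, 0.057; 2/10 v 7/10 gives 0.025, 0.072, 0.070.

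**Step 3: actual size.** For arms n₁, n₂ and common death rate π, size(π) = Σₐ Σ_b Bin(a; n₁, π) Bin(b; n₂, π) 1{p(a,b) < 0.05}, over all tables, with π from 0.01 to 0.99 in steps of 0.01.

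| Arms | Uncorrected, maximum | Corrected, maximum |
|---|---|---|
| 10:10 | 4.2% | 1.3% |
| 9:11 | 5.7% | 1.3% |
| 11:11 | 5.3% | 1.7% |
| 10:12 | 6.2% | 1.7% |
| 12:12 | 6.4% | 2.3% |

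At 10:10 the uncorrected size is 0.9% at 10% mortality, 3.0% at 20%, 3.7% at 30% and 4.0% at 40%.

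The unequal sizes are reachable. Twenty patients need not end on a complete block, so 9:11 can occur, and replacement of patients without microdialysis data takes the total above 20.

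**Step 4: power at 10:10 for an assumed 10% v 50%.** The same sum with the two rates unequal gives 0.471 uncorrected and 0.295 corrected. Boschloo's test at 10:10 rejects the same tables as the uncorrected test (size 4.2%, power 0.471). Fisher's test rejects the same tables as the corrected test (size 1.3%, power 0.295).

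**Step 5: the definition.** Take 0/10 v 4/10 and suppose that one of the four deaths is not due to TBI. Under Table 2 the result becomes 0/10 v 3/10: ad − bc = −30, the margins multiply to 10×10×3×17 = 5100, and the uncorrected statistic is 20×900/5100 = 3.53, p = 0.060 instead of 0.025.

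**The case against.** A reader might infer that chi-square fails to hold its error rate in this trial. At the planned 10:10 that is not so: the maximum is 4.2% uncorrected and 1.3% corrected. The excess elsewhere is modest, applies only to the uncorrected version, and is a maximum over death rates. At 12:12 it occurs at 50% mortality, and at 20% mortality the size there is 3.9%; at 9:11 and 20% mortality it is 5.3%. The article does not say how many patients will be added. Nor is the power gap a gap between chi-square and an exact test as such: at 10:10 the uncorrected chi-square and Boschloo's test reach the same decisions at 0.05. All of this stands.

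A reader might also infer that the text defines mortality as all deaths and so directly contradicts Table 2. It does not: it names no cause, and Table 2 could be read as supplying the detail. Nor do the documents support a claim of biased attribution, since investigators and caregivers are blinded throughout. Any death also scores 1 on the extended Glasgow Outcome Scale, so a non-TBI death is not lost from the trial.

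Finally, the choice of correction may be given in the additional files, and mortality is exploratory in a trial with no power calculation. That limits the weight of the point but does not remove it. The test that the article names is a large-sample one in about 20 patients, and the article's own text and table do not give the same mortality outcome.

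**Conclusion.** The point holds in a limited form and is minor. The chi-square test is a poor choice for this sample size because its p-value depends heavily on an option that the article does not state: 0.025 or 0.094 for the same data, and power of 0.47 or 0.30 for an assumed 10% v 50%. It is not a test that breaks the 5% level at 10:10. The uncorrected version does so modestly, up to about 6.4%, at nearby sizes that the randomization and replacement rules make possible. These figures rest on a two-sided 0.05 level and on assumed death rates, none of which the article gives.

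The mortality wording is a real mismatch on two counts, cause (restricted in Table 2, open in the text) and time (12 months in Table 2 only). Neither issue touches the ICP or cytokine analyses.

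**What to change.** In Study endpoints and in Statistical analysis, replace the chi-square test by an unconditional exact test (Boschloo or Barnard, one of them named) for binary outcomes. Add an exact confidence interval for the risk difference and state that the result is exploratory. Such a test controls size at whatever arm sizes result, and at 10:10 Boschloo's test loses no power against the uncorrected chi-square. Switching to Fisher's test would gain nothing over the corrected chi-square at 10:10.

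Reconcile Table 2 with the text by defining mortality as all-cause at 30 days and 12 months in both, with cause of death reported descriptively, so that no judgement of cause decides the event count.

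The cost is two sentences and one table cell. The test is available in R, and no extra patients are needed. Any change should be made before unblinding and logged as an amendment, because recruitment has been under way since March 2020.
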